#### G. Image-guidance for target localization

- After patient is set up on the treatment table, 2D (on-board imaging) and 3D CT (Cone-beam CT) systems that use x-rays will be used to align the patient with the treatment machine geometry based on the treatment plan. The alignment result will be evaluated by the attending physician and attending physicist and be approved for treatment by attending physician. The alignment data will be recorded. A rectal balloon can be used to immobilize the prostate.
- The initial localizations and alignment is based on the center of mass of the fiducial markers. Significant rotations may be corrected at initial localization stage, and intra-fractional rotations will be ignored. Further adjustment during the treatment will be translational shift of the center of mass determined via IGRT technique, using remote couch motion unless an institution has the ability to correct for rotations.
- For any image-guidance procedure, comparison with reference images or baseline data should be performed and reviewed by attending physician. The comparison can be done both manually and automatically. For any image-guidance method, if any deviation is larger than 2 mm, correction should be performed.

## 2. Supportive measures

### A. Urinary

- Symptomatic urinary medicines, (e.g. tamsulosin) are allowed at the discretion of the treating radiation oncologist or urologist.

### B. Bladder

- Patients will be asked to drink 400cc water 1 hour before the simulation and each treatment.

### C. Bowel

- Patients will be asked to empty the rectum before the simulation and each treatment. Dulcolax will be given and will be used when necessary for the purpose of emptying the rectum. Patients will be advised to adhere to a low gas, low motility diet commencing one day prior to the treatment.

### 3. Radiation therapy adverse events

- All patients will be seen weekly by their radiation oncologist during radiation therapy. Any observations regarding radiation reactions will be recorded and should include attention to the following potential side effects:
  - Small bowel or rectal irritation manifesting as abdominal cramping, diarrhea, rectal urgency, proctitis, or hematochezia; □
  - Bladder complications including urinary frequency/urgency, dysuria, hematuria, urinary tract infection, and incontinence;
  - Radiation dermatitis.
- Clinical discretion may be exercised to treat side effects from radiation therapy. Diarrhea/rectal frequency/urgency may be managed with diphenoxylate or loperamide. Bladder irritation may be mitigated with phenazopyridine. Urinary frequency/urgency can be managed with anticholinergic agents or alpha-blockers such as tamsulosin. Erectile dysfunction can be managed with phosphodiesterase (PDE) inhibitors such as sildenafil.
- Adverse Events (AEs) and Serious Adverse Events (SAEs) Reporting Requirements
  - **Definition of an AE:** Any unfavorable and unintended sign (including an abnormal laboratory finding), symptom, or disease temporally associated with the use of a medical treatment or procedure regardless of whether it is considered related to the medical treatment or procedure (attribution of unrelated, unlikely, possible, probable, or definite). [CTEP, NCI Guidelines: Adverse Event Reporting Requirements. January 2005;
  - **Definition of an SAE:** Any adverse experience occurring during any part of protocol treatment and 30 days after that results in any of the following outcomes:
    - ◆ Death;
    - ◆ A life-threatening adverse experience;
    - ◆ Inpatient hospitalization or prolongation of existing hospitalization;
    - ◆ A persistent or significant disability/incapacity;
    - ◆ A congenital anomaly/birth defect.
- Important medical events that do not result in death, are not life threatening, or do not require hospitalization may be considered an SAE, when, based upon medical judgment, they may jeopardize the patient and may require medical or surgical intervention to prevent one of the outcomes listed in the definition. Any pregnancy occurring on study must be reported via CCTU as a medically significant event.

### 6.0 Hormonal therapy

Neoadjuvant androgen deprivation (ADT) will be given to intermediate risk patients (T2b-c or GS 7 or PSA 10-20) before the start of radiotherapy. Two injections of ADT (every 3 months) will be given prior radiotherapy and the radiotherapy will be started 1 month after the last injection of ADT.

- Distant metastasis will be documented if clinical or bone scan evidence is demonstrated. Ultrasound evaluation of the prostate with needle biopsy as indicated by the findings is recommended at the time distant metastasis is reported.
  - Regional metastasis will be documented if there is radiographic evidence (CT or MRI) of lymphadenopathy and histologic confirmation.

## **8.0 Statistical consideration**

1. Primary endpoint
  - Evaluate and compare the HRQOL by the proportion of patients with > 5-point and > 2-point reductions in the EPIC bowel and urinary domains, respectively, at 1 year

compared with baseline, between the two treatment arms.

2. Secondary endpoint
  - Rate of acute and late GI and GU toxicity for each arm at 1, 2, and 5 years
  - Biochemical failure-free survival
  - Disease-specific survival
  - Overall survival
3. Sample size derivation and accrual
  - The primary goal of this phase II study is to comparing the SBRT and IMRT. The choice of regimen will be based on maintaining acceptable patient reported HRQOL from baseline. There will be two co-primary endpoints based on summary scores from the bowel and urinary domains of the EPIC questionnaire. Although HRQOL is collected at multiple time points, it has been decided that EPIC information collected at 1 year will be compared to baseline EPIC data to calculate the sample size and to test the primary hypothesis. In part, this is due to missing data issues with patient reported outcome data and it is more likely to have full HRQOL patient information earlier in the study (e.g., 6 months, 1 year) than later (e.g., 2 years on). The hypothesis for each arm is that the probability of the change in EPIC HRQOL scores (1-year minus baseline) is less than (or equal to) an acceptable limit. Thus, for each arm, the hypotheses are:

$$H_0 : p \leq p_0 \quad \text{v.s.} \quad H_1 : p > p_a$$

where  $p_0$  is the probability under the null hypothesis.

From the conventional arm of RTOG 0415, in an analysis of 108 patients (mean pretreatment score 94 with SE=9 and range 61-100), 38 patients (35%) had a change in EPIC bowel domain score (baseline to 1-year) that was worse than 5 points. For 110 patients (mean pretreatment score 88, SE=12, range 35-100), 43 (39%) had a change in EPIC urinary domain score that was worse than 2 points. Mean reduction in bowel and urinary scores have also been published in a historical series by Wei et al. (2002). The mean reduction in bowel and urinary scores observed in the RTOG 0415 analysis are in keeping with the series published by Wei. Standard radiotherapy in regimens such as used in the conventional arm of 0415 is well tolerated. Thus the HRQOL analysis from the 0415 study will be used in the sample size calculation. The percentage of patients with change in EPIC bowel domain score (baseline to 1-year) that was worse than 5 points and a change in EPIC urinary domain score that was worse than 2 points are felt to be clinically meaningful endpoints to assess for tolerability and safety.

A rate for the worse-than-5 point change in bowel score of up to 35% of patients will be considered acceptable, with a rate  $\geq 60\%$  specified as unacceptable. Similarly, a rate for the worse-than-2 point change in urinary score of up to 40% will be considered acceptable, with a rate  $\geq 65\%$  unacceptable. Using the normal approximation to the binomial distribution for  $p$ , the formula to calculate the sample size is given by:

$$n = \left[ \frac{z_{1-\alpha} \sqrt{p_0(1-p_0)} + z_{1-\alpha} \sqrt{p_a(1-p_a)}}{(p_0 - p_a)} \right]^2$$

where  $p_0$  is as previously defined,  $p_a$  = the alternative probability,  $z_q$  = 100(qth) percentile of the standard normal distribution. With the aforementioned design parameters, a sample size of 60 eligible patients (30 per arm) is required with 80% power and significance level 0.025 (one-sided test). The significance level 0.025 will be used for each endpoint in order to preserve an overall significance level of 0.05. Adjusting for 5% ineligibility, **the required sample size is 64 patients (32 per arm).**

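### The 80% power in section 8.0 has essentially no reserve for missing EPIC questionnaires; the printed sample-size formula contains a misprint, and the z-test does not hold 0.025 exactly for the bowel domain

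*Protocol*

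**What the plan says.** Protocol section 8.0, item 3 (sample size derivation and accrual), tests each arm on its own against fixed limits, in two EPIC domains. For bowel, "A rate for the worse-than-5 point change in bowel score of up to 35% of patients will be considered acceptable", and 60% or more is unacceptable. For the urinary domain, "a rate for the worse-than-2 point change in urinary score of up to 40% will be considered acceptable", and 65% or more is unacceptable. The method is the normal approximation to the binomial. The section prints a formula with the same quantile, z(1-alpha), in both terms of the numerator. It then concludes that "a sample size of 60 eligible patients (30 per arm) is required with 80% power and significance level 0.025 (one-sided test"). On multiplicity it says: "The significance level 0.025 will be used for each endpoint in order to preserve an overall significance level of 0.05". The figure is raised to 64 patients (32 per arm) for 5% ineligibility and for nothing else.

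The same item explains why the 1-year time point was chosen: in part, "this is due to missing data issues with patient reported outcome data".

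Item 4 (analysis of primary endpoint) specifies a one-sample z-test at 0.025 per endpoint in each arm. A rejection in either domain makes the regimen unacceptable. If neither domain rejects, the regimen is acceptable.

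**The concern.** The endpoint is a change from baseline to 1 year, so a patient counts only if both questionnaires exist. A calculation that needs 30 such patients, and whose only inflation is used up by ineligibility, has no expected margin for missing forms. Yet the section itself treats missing forms as a known problem.

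The direction of the error matters here. The null hypothesis is that the regimen is acceptable, and not rejecting it is read as a positive finding. Loss of power therefore makes the trial more lenient: a regimen at the protocol's own unacceptable rate in one domain is more likely to pass.

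Two further statements in the same section do not match what it prints or plans. The formula has no term for power, so it cannot yield a sample size for 80% power. And with about 30 binary outcomes per arm, a z-test without continuity correction need not hold the 0.025 level on which the stated overall 0.05 rests.

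**Working it through.** **Inputs** (all from section 8.0, items 3 and 4): bowel p0 = 0.35, pa = 0.60; urinary p0 = 0.40, pa = 0.65; one-sided alpha 0.025, so z(1-alpha) = 1.960; power 80%, so z(1-beta) = 0.842; 30 eligible and 32 enrolled per arm. The missing-EPIC rate is an assumption, because the protocol gives none.

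**Reproducing the stated figure.** With s0 = √(p0(1−p0)) and sa = √(pa(1−pa)), and z(1-beta) in the second term:

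- n = [(1.960·s0 + 0.842·sa)/(pa − p0)]²
- Bowel: [(1.960×0.4770 + 0.842×0.4899)/0.25]² = (1.3472/0.25)² = 29.04, rounded up to 30
- Urinary: [(1.960×0.4899 + 0.842×0.4770)/0.25]² = (1.3616/0.25)² = 29.66, rounded up to 30
- Inflation: 60/0.95 = 63.2, taken to 64, or 32 per arm

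So 30 per arm and 64 in total both reproduce.

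**Formula as printed**, with z(1-alpha) twice: [1.960×(0.4770 + 0.4899)/0.25]² = (1.8950/0.25)² = 57.46, or 58 per arm, in both domains.

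**Power as questionnaires are lost.** Power = Φ[(0.25√n − 1.960·s0)/sa]. At n = 30 this is 81.2% (bowel) and 80.4% (urinary). After 5% ineligibility, 32 × 0.95 = 30.4 eligible patients remain per arm. Multiplying by (1 − missing rate):

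| Missing EPIC (assumed) | Evaluable per arm | Bowel power | Urinary power |
|---|---|---|---|
| 5% | 28.9 | 79.8% | 78.9% |
| 10% | 27.4 | 77.7% | 76.7% |
| 15% | 25.8 | 75.4% | 74.3% |
| 20% | 24.3 | 72.9% | 71.6% |

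In whole patients, n = 27 gives 77.1% and 76.1%, and n = 24 gives 72.3% and 71.0%.

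**Exact behaviour of the planned z-test at n = 30** (binomial tails):

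- Bowel: 15/30 gives z = 1.72 and 16/30 gives z = 2.11, so it rejects at 16 or more. P(X ≥ 16 | 0.35) = 0.0301; P(X ≥ 16 | 0.60) = 82.5%.
- Urinary: 17/30 gives z = 1.86 and 18/30 gives z = 2.24, so it rejects at 18 or more. P(X ≥ 18 | 0.40) = 0.0212; P(X ≥ 18 | 0.65) = 78.0%.
- Sum of the two sizes: 0.0301 + 0.0212 = 0.0513. This is the Bonferroni bound on the overall level within an arm.

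**Exact binomial test, for comparison.** Holding bowel at or below 0.025 with n = 30 means rejecting at 17 or more: size 0.0124, power 71.5%. The urinary cut-off of 18 already satisfies 0.025.

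**The case against.** The best defence is that the planned figures do follow from the planned method. The protocol says it uses the normal approximation, and on that basis 30 per arm gives at least 80% power in both domains. This stands. A reader who puts numbers into the printed formula might infer that the trial needs 58 per arm and is badly undersized. The documents do not support that: 80% power is stated, power can enter only through a beta term, and with that term the stated 30 appears. The repeated subscript is an evident misprint with no effect on the design.

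The z-test discrepancies are also modest. A bowel size of 0.030 against 0.025 is ordinary binomial discreteness. Bowel power of 82.5% exceeds the target, and urinary power of 78.0% is within two points of it.

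On missing data, a reader might infer that a single missing form breaks the calculation. It does not: if nobody is ineligible, two missing forms per arm are absorbed, and at 5% missing the loss is trivial. Choosing the 1-year time point also reduces missingness. How missing scores are handled in the analysis is commonly left to the SAP, so the lack of such a rule here is not the point.

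What the defence does not answer is that the protocol itself fixes the sample size and the power claim, names missing questionnaires as a problem, and makes no allowance for them.

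**Conclusion.** The point holds in a limited form. The power claim rests on nearly every eligible patient supplying both questionnaires. If 10% to 20% do not, per-domain power is about 77% to 72% for bowel and 76% to 71% for urinary. These figures rest on the assumed missing rate, on 5% ineligibility occurring as planned, and on the normal approximation. The formula needs correcting, but the sample size does not follow from the misprint and is not wrong. The claim that 0.025 per endpoint preserves 0.05 overall is not exactly met: the bowel size is 0.030, and the two sizes sum to 0.051 instead of at most 0.05.

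Two stronger conclusions should not be drawn. Per-domain power cannot be turned directly into the chance that an unacceptable regimen passes. Since either domain can reject, the two roughly correspond only when one domain is bad; when both are bad, the chance of detection is at least as high as in either domain alone. Nor can an exact test's power be taken as the plan's. An exact test at n = 24 would have 65.0% power for bowel, but the protocol does not plan one.

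**What to change.** In section 8.0, item 3:

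- Replace the second z(1-alpha) by z(1-beta).
- State an assumed rate of missing baseline or 1-year EPIC and restate power for the resulting evaluable number, for example about 77%/76% at 27 per arm and 72%/71% at 24.
- Report the exact size and power of the planned z-test at 30 per arm (bowel 0.030 and 82.5%, urinary 0.021 and 78.0%), and drop the claim that 0.025 and 80% are held.

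An exact binomial test in item 4 would hold 0.025, but it is a trade-off and not a plain improvement: at n = 30 it lowers bowel power from 82.5% to 71.5%, which increases the risk of passing an unacceptable regimen. If the sponsor prefers it, that cost should be stated.

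The change costs a few restated figures and a less favourable stated power; no extra patients are needed. Should the sponsor choose instead to keep 30 evaluable, enrolment would be 30/(0.95×0.90) = 35.1, or 36 per arm, at 10% missing, and 30/(0.95×0.80) = 39.5, or 40 per arm, at 20%.

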#### 4. Analysis of primary endpoint

- The co-primary endpoints are: (1) the proportion of patients with change from baseline to the 1-year EPIC bowel domain score that exceeds 5 points; and (2) the proportion of patients change from baseline to 1-year EPIC urinary domain score that exceeds 2 points. Analysis will be done separately for each arm. The average score of each arm will be calculated, along with the standard error, based on the hypothesis

$$H_0 : p \leq p_0 \quad v.s. \quad H_1 : p > p_a$$

- The one-sample z-test for proportion with significance level of 0.025 (for each endpoint) will be used to test the hypothesis.
- For a given arm, if  $H_0$  is rejected for either EPIC domain, then it will be concluded that the regimen given on that arm is unacceptable in terms of PRO. However if it is not rejected for both domains, then that regimen will be considered acceptable. If both arms yield an acceptable result, then consideration may be given to using other factors, specifically, results of secondary endpoints to decide if one regimen is more acceptable than the other one. In each arm, logistic regression will be performed, both an unadjusted and adjusted analysis. In the adjusted analysis, the variables in the regression will at least include the stratification variable, treatment modality, and, if appropriate, additional variables such as Gleason score, PSA, age and race can be included.

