### Objectives

#### Primary Objective

- To compare the 1-year health-related quality of life (HRQOL) between SBRT and IMRT as measured by the Bowel and Urinary domains of the Expanded Prostate Cancer Index Composite (EPIC) instrument.

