## **2.0 Objectives**

### **Primary Objective**

- To compare the 1-year health-related quality of life (HRQOL) between SBRT and IMRT as measured by the Bowel and Urinary domains of the Expanded Prostate Cancer Index Composite (EPIC) instrument.

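### The primary objective is to compare SBRT with IMRT, but the primary decision rule tests each arm only against a historical limit, and the one regression naming treatment is set up so that its effect cannot be estimated

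*Protocol*

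**What the plan says.** The comparative aim appears in several places. The Primary Objective, in both the Protocol Summary and section 2.0, is "To compare the 1-year health-related quality of life (HRQOL) between SBRT and IMRT as measured by the Bowel and Urinary domains" of the EPIC. Section 8.0, item 1 defines the endpoint as the proportions of patients worsening by more than 5 points (bowel) and more than 2 points (urinary) at 1 year, "compared with baseline, between the two treatment arms". Item 3 opens with "The primary goal of this phase II study is to comparing the SBRT and IMRT".

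The hypotheses in items 3 and 4 are nevertheless set for each arm alone, as p no greater than a fixed p0. For bowel, "A rate for the worse-than-5 point change in bowel score of up to 35% of patients will be considered acceptable"; the urinary limit is 40%. Both come from the conventional arm of RTOG 0415 (38 of 108 and 43 of 110 patients). Item 4 states "Analysis will be done separately for each arm" and "The one-sample z-test for proportion with significance level of 0.025 (for each endpoint) will be used to test the hypothesis". The decision is also per arm: if the null is "rejected for either EPIC domain, then it will be concluded that the regimen given on that arm is unacceptable in terms of PRO". If both arms pass, the secondary endpoints may be considered in choosing between them; the secondary objectives are themselves worded as estimates for each arm.

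Item 4 also describes unadjusted and adjusted logistic regressions, to be run in each arm. The adjusted model is to include at least the stratification variable and treatment modality.

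**The concern.** A trial randomised between two regimens, with a comparative objective, needs some between-arm estimate on its primary endpoint. The decision rule here produces two separate verdicts, and nothing in it measures how far apart the arms are. Item 3 says the choice of regimen will rest on acceptable patient-reported outcome, so one arm passing and the other failing bears directly on which regimen is preferred. Yet two verdicts can differ when the data barely do, and can agree when the data differ widely. The regression that might have supplied the comparison is specified so that it cannot.

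**Working it through.** **Inputs (Protocol 8.0, items 3 and 4).** Bowel p0 = 0.35, pa = 0.60; urinary p0 = 0.40, pa = 0.65; one-sided 0.025 per endpoint; 80% power; 30 eligible per arm, 32 after 5% ineligibility. Assumed here: 30 evaluable per arm, null-variance z-test without continuity correction, independent arms.

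**1. The plan's own sample size.** n = [(z(0.975)·√(p0(1−p0)) + z(0.80)·√(pa(1−pa))) / (pa−p0)]².
- Bowel: 29.04. Urinary: 29.66. Both round up to 30 per arm, and 30/0.95 = 31.6 gives 32 per arm, 64 in total.

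The stated figure is therefore reproduced as a one-sample size. (The printed formula has the significance quantile in both terms, which would give 57.5; the stated 30 needs the power quantile in the second term. That is a separate matter.)

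**2. Cut-offs.** Reject when (x/30 − p0)/√(p0(1−p0)/30) > 1.96.
- Bowel: x = 15 gives z = 1.72; x = 16 gives 2.11. Reject at 16/30 or more.
- Urinary: x = 17 gives z = 1.86; x = 18 gives 2.24. Reject at 18/30 or more.

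**3. Two outcomes on the bowel domain.**

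| Counts | Verdicts on bowel | Fisher p between arms |
|---|---|---|
| 16/30 vs 15/30 | unacceptable vs acceptable | 1.0 |
| 15/30 vs 5/30 | acceptable vs acceptable | 0.013 |

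**4. Opposite verdicts when the arms are truly identical.** Let b and u be the exact binomial probabilities of rejecting for bowel and urinary, and r the probability that an arm is called unacceptable. Then P(opposite verdicts) = 2r(1−r). The correlation between domains is not given, so r is bracketed: r = max(b, u) for fully dependent domains and r = 1 − (1−b)(1−u) for independent ones.

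| True rates (bowel/urinary), both arms | b | u | Fully dependent | Independent |
|---|---|---|---|---|
| 35%/40% | 0.030 | 0.021 | 5.8% | 9.6% |
| 45%/50% | 0.231 | 0.181 | 35.5% | 46.6% |
| 47.5%/52.5% | 0.323 | 0.262 | 43.8% | 50.0% |
| 60%/65% | 0.825 | 0.780 | 28.9% | 7.4% |

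**5. The regression.** Within one arm every patient has the same treatment, so a treatment term is a constant and has no estimable coefficient. The term makes sense only in a model pooling both arms. Running the model in each arm and including treatment modality cannot both stand.

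**6. What a between-arm estimate would offer at this size.** Half-width = z·√(2p(1−p)/30).
- 95% (z = 1.96): 24.1 points at p = 0.35, 24.8 at 0.40, 25.3 at 0.50.
- 97.5% (z = 2.24): 27.6, 28.4 and 28.9 points.
- Power for 35% vs 60% with 30 per arm: 49% at two-sided 0.05, 38% at two-sided 0.025. For 80% power at two-sided 0.025, about 75 evaluable per arm would be needed.

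**The case against.** Parallel evaluation of randomised arms against fixed acceptability limits is a recognised phase II design. Item 3 states that purpose, and the sample size follows from it. This stands: the one-sample tests are not wrong in themselves, and the fault is that objective, endpoint and goal are worded as a comparison the decision rule does not make.

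A reader might infer that the stratification is ignored and that no between-arm analysis was ever contemplated. The text does not support that. Item 4 puts both the stratification variable and treatment modality into the adjusted regression, which suggests a pooled model was intended. What can be said is that it is specified contradictorily and carries no weight in the decision.

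A reader might also infer that the per-arm tests must be replaced by a formal between-arm primary test. That does not follow either. It would exchange an analysis planned at 80% power for one with about 38%, and rewording the objective would also remove the mismatch.

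Two cautions on size also stand. The highest discordance figures arise only when the true rates lie between the acceptable and unacceptable limits, where any threshold rule is close to a coin toss. And the Protocol does not itself say that differing verdicts show a difference between regimens; it concludes only about the regimen on that arm. The risk is that, under a comparative objective, nothing in the plan guards against that reading.

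**Conclusion.** The concern holds as a mismatch. The plan, followed exactly, yields two acceptability verdicts and no usable estimate of the SBRT–IMRT difference on the primary endpoint, so it does not answer its stated objective. The size depends on the true rates. For identical arms, opposite verdicts are expected in about 6–10% of trials at the acceptable limits, 36–47% at 45%/50%, 44–50% at 47.5%/52.5%, and 7–29% at the unacceptable rates. These ranges rest on 30 evaluable per arm and run between fully dependent and independent domains. The reverse failure also exists: a 33-point difference in bowel worsening (15/30 vs 5/30) passes both arms on that domain. The contradiction in the regression needs no assumption.

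**What to change.** In section 8.0, item 4:
- Replace the regression within each arm by one pooled model per domain with treatment and risk group.
- Report the SBRT-minus-IMRT difference in the proportion worsening for each domain with a 97.5% CI, labelled as estimation.
- Keep the one-sample z-tests as per-arm acceptability screens, and state that differing verdicts are not evidence that the arms differ.
- State the limits: a half-width of about 28–29 points at 97.5% (24–25 at 95%), and about 38% power at two-sided 0.025 (49% at 0.05) for 35% vs 60%.

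Alternatively, restate the primary objective, endpoint and goal as acceptability of each arm against the historical limits, and still correct the regression sentence.

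The first option costs wording and one analysis of data already collected, with no extra patients; the price is openly reporting a wide interval. The second costs only wording, but gives up the comparative claim.

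### The logistic regression is confined to each arm yet must include treatment modality, which is constant within an arm, so the required model cannot be fitted as written

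*Protocol*

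**What the plan says.** The primary objective (Protocol Summary and section 2.0) is to compare 1-year quality of life between SBRT and IMRT. Section 8.0, item 1 also words the primary endpoint as a comparison between the arms, using the proportions of patients with "> 5-point and > 2-point reductions in the EPIC bowel and urinary domains".

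Item 4 of section 8.0 then sets out the analysis. It opens with the rule "Analysis will be done separately for each arm" and names the test: "The one-sample z-test for proportion with significance level of 0.025 (for each endpoint) will be used to test the hypothesis". An arm is judged unacceptable if its null hypothesis is rejected in either domain.

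The same item adds a regression: "In each arm, logistic regression will be performed, both an unadjusted and adjusted analysis". Its content is fixed in the next sentence: "In the adjusted analysis, the variables in the regression will at least include the stratification variable, treatment modality". Further covariates are optional: "if appropriate, additional variables such as Gleason score, PSA, age and race can be included". The design table in the Protocol Summary gives one radiotherapy schedule per arm and names risk group as the only stratification factor.

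**The concern.** Two adjacent sentences in item 4 cannot both be followed. The first fits the model inside one arm. The second requires a term for treatment, which has a single value inside that arm. A constant covariate duplicates the intercept, so no treatment effect can come out of the model.

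What is at stake is the stated comparison. The only primary test sets each arm against a fixed limit, and the regression is the only analysis of the primary endpoint that names treatment as a variable. If it cannot be fitted as written, the protocol has no usable between-arm estimate for the endpoint that it describes as a comparison. An analyst would have to choose the model later, in an open-label trial with a patient-reported outcome.

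**Working it through.** **1. The plan's own figure.** Inputs from section 8.0, item 3: bowel limits 0.35 (acceptable) and 0.60 (unacceptable), urinary limits 0.40 and 0.65, one-sided 0.025, 80% power. One-sample formula:

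n = [(z(0.975) × √(p0(1−p0)) + z(0.80) × √(pa(1−pa))) / (pa−p0)]²

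- Bowel: [(1.960 × 0.4770 + 0.8416 × 0.4899) / 0.25]² = 29.04, rounded up to 30.
- Urinary: [(1.960 × 0.4899 + 0.8416 × 0.4770) / 0.25]² = 29.66, rounded up to 30.
- Ineligibility: 60 / 0.95 = 63.2, giving 64 (32 per arm).

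These match the protocol. (The formula as printed repeats the significance-level percentile where the power percentile belongs and would give 58 per arm, so that is evidently a misprint.) The sample size is thus built on single-arm tests and does not depend on the regression.

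**2. Can the required model be fitted?** The required columns are intercept, risk group and treatment. For illustration, take 30 patients per arm with 15 in each risk group; the split does not matter as long as both groups are present.

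| Data used | Columns | Rank | Treatment coefficient |
|---|---|---|---|
| IMRT arm only | 3 | 2 | not estimable |
| SBRT arm only | 3 | 2 | not estimable |
| Both arms pooled | 3 | 3 | estimable |

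**3. Could treatment modality mean something else?** The other candidate is hormonal therapy. Section 6.0 plans it for intermediate-risk patients, so as planned that term would duplicate risk group, which is also required. On either reading one required term is redundant within an arm.

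**4. What would a pooled model deliver?** Take 30 per arm and true rates of 35% and 60%. Rates of 40% and 65% give the same results by symmetry.

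- Odds ratio = (0.60/0.40) / (0.35/0.65) = 2.79.
- Standard error of its log = √[1/(30 × 0.35 × 0.65) + 1/(30 × 0.60 × 0.40)] = √(0.1465 + 0.1389) = 0.534.
- Approximate 95% confidence interval: exp(1.0245 ± 1.96 × 0.534) = 0.98 to 7.94.
- Power at two-sided 0.05, with mean rate 0.475: Φ[(0.25 − 1.96 × √(2 × 0.475 × 0.525/30)) / √((0.2275 + 0.24)/30)] = Φ[(0.25 − 0.2527)/0.1248] = Φ(−0.022) = 49%.
- With two-sided 0.025 (z = 2.241) the same formula gives 38%.
- Patients per arm for 80% power at two-sided 0.05: [1.96 × √0.49875 + 0.8416 × √0.4675]² / 0.25² = 61.4, so 62.

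**5. Events available.** At the acceptable rates each arm has about 30 × 0.35 = 10.5 to 30 × 0.40 = 12 events. Two arms pooled have 21 to 24, or 7 to 8 per term for arm, risk group and baseline score.

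**The case against.** The strongest defence is that the regression is secondary to the decision. It does not enter the acceptability rule in item 4 or the sample size. A competent analyst would see that treatment belongs only in a pooled model, and a statistical analysis plan could say so. What stands is that the consequence is limited. What does not stand is that this is detail left open: the protocol itself fixes both the level of the analysis and the required term, so a later plan must depart from one of them.

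Several stronger readings are tempting, and the document does not support them.

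- **That baseline EPIC score is wrongly excluded.** The required list is a minimum and the optional list is open. Adding baseline score is an improvement, not the correction of an error.
- **That baseline imbalance between arms distorts the planned tests.** Each arm is tested against a fixed limit, and no planned test compares the arms. Imbalance matters only once a between-arm model is fitted.
- **That baseline adjustment would buy a large gain in power.** The planned outcome is already a change from baseline, and the protocol gives no correlation between baseline and 1-year scores from which to size a gain.
- **That improvements would be counted as failures.** Item 4 speaks of "the proportion of patients with change from baseline to the 1-year EPIC bowel domain score that exceeds 5 points" without a direction, and item 3 takes change as the 1-year score minus baseline. Item 1 says reductions, and the sample-size text counts worsening, so the intent is clear.
- **That race, PSA and Gleason score should go.** They are optional. PSA and Gleason score can carry information within a two-level risk group, and eligibility does not restrict race.
- **That nothing can be fitted within an arm.** Prognostic models of risk group, age or PSA could be. What fails is the treatment term.

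**Conclusion.** The contradiction is certain: it follows from the two sentences and from having one treatment per arm, with no numerical assumption. The required model cannot be fitted as written, and the stated between-arm comparison is left without a workable analysis of the primary endpoint.

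The size is moderate. The per-arm z-tests, the decision rule and the 64-patient sample size all stand. Even when repaired, the regression can only be supportive, with about 49% power at two-sided 0.05 for 35% versus 60%. That figure assumes 30 evaluable patients in each arm, true rates at the protocol's own limits and the normal approximation, before covariate adjustment. The point should be fixed, but it is not a ground for doubting the planned per-arm decision.

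**What to change.** In section 8.0, item 4, delete the opening phrase that confines the logistic regression to each arm. In its place, specify:

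- one logistic model per domain, fitted to both arms together;
- as outcome, a reduction from baseline to 1 year of more than 5 points (bowel) or more than 2 points (urinary), so that the direction is explicit;
- an unadjusted model with arm alone, and an adjusted model with arm, risk group and, as a free improvement, the baseline EPIC domain score;
- the odds ratio for arm with a 95% confidence interval, labelled supportive and kept outside the acceptability rule.

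The optional covariates can stay optional. If the sponsor prefers per-arm models, the treatment term must be removed; they would then be prognostic only, and the between-arm comparison would still lack an analysis.

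The cost is a few sentences. Baseline EPIC is already mandatory under section 7.0, 1-year EPIC is already scheduled, and risk group is known at randomisation. No extra patients or visits are needed.
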